9.4 Timeline for individual study participants

[figure not shown]

2 : Flowchart of the schedule for individual study participants

| Examination | Duration |
| --- | --- |
| Neurocognitive testing | 15 |
| PCFS score, Chalder Fatigue Scale, Bell Score, MFI-20 | 10 minutes |
| MRC score | 5 |
| Blood sample | 5 |
| Measurement of vital signs | 10 |

Table3 : Duration of examinations in the evaluation examination block

| Examination | Duration |
| --- | --- |
| Inpatient stay | 7 days, including the following measures |
| Neurocognitive testing | 15 minutes |
| PCFS score, Chalder Fatigue Scale, Bell Score, MFI-20 | 10 |
| MRC score | 5 |
| Blood sample | 5 |
| Measurement of vital signs | 10 |
| Neurological examination | 15 |
| Spirometry | 10 |
| If venous cannulation is not possible: Shaldon device | 15 |
| Venous cannulation | 5 |
| Extracorporeal therapy 1 | 240 |
| Venous cannulation | 5 |
| Extracorporeal therapy 2 | 240 |
| Venous cannulation | 5 |
| Extracorporeal therapy 3 | 240 |
| Rest day |  |
| Extracorporeal therapy 4 | 240 |
| Day off |  |
| Extracorporeal therapy | 240 |

Table4 : Duration of examinations and interventions in the block "7-day inpatient stay for therapy cycle 1" and "9-day inpatient stay for therapy cycle 2"; blood samples indicated above as being taken before or after therapy are taken during extracorporeal therapy to avoid additional punctures.

| Examination | Duration |
| --- | --- |
| Medical history interview | 30 |
| Neurocognitive testing | 15 |
| PCFS score | 10 minutes |
| MRC score | 5 |
| Blood sampling | 5 |
| Measurement of vital signs | 10 |
| Neurological examination | 15 |
| Spirometry | 10 |

Table5 : Duration of examinations in the "Follow-up visit 4 weeks" block

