## **6. Target parameters**

6.1 Primary endpoints:

Effectiveness of immunoadsorption on symptom burden in patients with post-COVID syndrome measured by the values of:

- Post-COVID-19 functional status scale (PCFS)
- Chalder Fatigue Scale
- Montreal Cognitive Assessment (MOCA)
- MFI-20
- Bell Score
- Strength measurement

and comparison before and after active treatment and before and after sham treatment (before treatment cycle 1/after treatment cycle 1 and before treatment cycle 2/after treatment cycle 2).

6.2 Secondary endpoints:

- Frequency of adverse events under active and sham treatment
- Prevalence of anti-adrenergic and anti-muscarinic autoantibodies in patients with post-COVID syndrome:
  - Proportion of subjects with evidence of anti-α1-adrenoreceptor Abs
  - Proportion of subjects with evidence of anti-α2-adrenergic receptor Abs
  - Proportion of subjects with evidence of anti-β1-adrenoreceptor Abs
  - Proportion of subjects with evidence of anti-β2-adrenergic receptor Abs
  - Proportion of subjects with evidence of anti-β3-adrenoreceptor Abs
  - Proportion of subjects with evidence of anti-M1 acetylcholine receptor Abs
  - Proportion of subjects with evidence of anti-M2 acetylcholine receptor Abs
  - Proportion of subjects with evidence of anti-M3 acetylcholine receptor Abs
  - Proportion of subjects with evidence of anti-M4 acetylcholine receptor Abs
- Concentration of:
  - Anti-α1-adrenoreceptor Abs
  - Anti-α2-adrenoreceptor Abs
  - Anti-β1-adrenoreceptor Abs
  - Anti-β1 adrenoreceptor Abs
  - Anti-β1 adrenoreceptor Abs
  - Anti-M1 acetylcholine receptor Abs
  - Anti-M2 acetylcholine receptor Abs
  - Anti-M3 acetylcholine receptor Abs
  - Anti-M4 acetylcholine receptor Abs

Before and after active and sham treatment (before therapy cycle 1/after therapy cycle 1 and before therapy cycle 2/after therapy cycle 2).

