| Antibodies against muscarinic acetylcholine receptors of subtypes M1-M4 | E, vT1, nT1, vT2, nT2 | Serum |
| Venous blood gas analysis | E, T1, T2 | Whole blood |
| Activated partial thromboplastin time (aPTT) | E, vT1, nT1, vT2, nT2 | Citrate plasma |
| International normalized ratio (INR) | E, vT1, nT1, vT2, nT2 | Citrate plasma |
| Fibrinogen concentration | E, vT1, nT1, vT2, nT2 | Citrate plasma |
| Albumin in spontaneous urine | E, vT1, nT1, vT2, nT2 | Midstream urine |
| Creatinine in spontaneous urine | E, vT1, nT1, vT2, nT2 | Midstream urine |
| Total protein in spontaneous urine | E, vT1, nT1, vT2, nT2 | Midstream urine |
| Urine sediment including acanthocyte concentration | E, vT1, nT1, vT2, nT2 | Midstream urine |
| Albumin/creatinine ratio in spontaneous urine | E, vT1, nT1, vT2, nT2 | Midstream urine |
| Total protein/creatinine ratio in spontaneous urine | E, vT1, nT1, vT2, nT2 | Midstream urine |

1 table: Overview of the parameters determined from the respective biomaterial and the time of material collection (E = evaluation tests; T1 = during therapy cycle 1; T2 = during therapy cycle 2; vT1 = before therapy cycle 1; nT1 = after therapy cycle 1; vT2 = before therapy cycle 2; nT2 = after therapy cycle 2).

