| Anthropometry | Yes | E |
| Vital signs (HR, RR, temp., respiratory rate) | no | E, T1, T2 |
| 12-channel ECG | Yes | E |
| Spirometry | Yes | E, nT1, vT2, nT2, F |
| Neurological examination | Yes | E, nT1, vT2, nT2, F |
| Neurocognitive testing | Yes | E, nT1, vT2, nT2, F |
| PCFS score | No | E, nT1, vT2, nT2, F |
| Chalder fatigue scale | no | E, nT1, vT2, nT2, F |
| Bell score | No | E, nT1, vT2, nT2, F |
| MRC score | no | E, nT1, vT2, nT2, F |
| Blood sampling | yes | E, T1, nT1, T2, vT2, nT2, F |
| Urine analysis | Yes | E, nT1, vT2, nT2, F |
| Cranial MRI | yes | E |
| Psychological questionnaires | yes | E, nT1, vT2, nT2, F |

Table2 : Overview of examinations performed, proportion of examinations whose results can be used from the Gutenberg Long COVID study as part of the evaluation examinations, and when the respective examinations are performed. (E = evaluation examinations; T1 = during therapy cycle 1; T2 = during therapy cycle 2; vT1 = before therapy cycle 1; nT1 = after therapy cycle 1; vT2 = before therapy cycle 2; nT2 = after therapy cycle 2, F = follow-up; for most examinations, the evaluation examination is equivalent to the examination before therapy cycle 1).

- 1. Informing participants about examination results

After each examination, the test subjects will receive brief information if there are any relevant examination results. After completion of the study, participants will receive a detailed written report of the findings and an appointment will be offered to discuss the findings.

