## 9.5 Administration of treatment

All study participants receive 5 blinded extracorporeal therapies with the Plasauto Sigma from Diamed with a TR-350 adsorber inserted and 5 extracorporeal therapies with the same device with no adsorbers inserted. The order, i.e., whether the verum treatment (adsorber inserted) or the sham treatment with no adsorbents is performed first, will be assigned randomly. Immunoadsorption and sham treatment are performed, depending on the condition of the veins, via two large-lumen peripheral venous cannulas or, if this is not possible due to poor vein condition, via a Shaldon catheter, which is inserted into the right or left internal jugular vein under ultrasound guidance after the patient has been informed of the risks and has given their consent. Anticoagulation is performed during both sham treatment and actual immunoadsorption using heparin (bolus of 2000iE, then flow rate of 2000iE/h) and the PA-420 tube system is used. The blood flow is set to 60 ml/min and the plasma flow to 20ml/min for both therapies. The exchange volume depends on the patient's size and body weight and is 2-2.5 L per session.

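### The Table 4 caption places the before- and after-therapy blood samples during extracorporeal therapy, contradicting the endpoint definition and the sampling codes

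*Protocol*

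**What the plan says.** Section 6.2 of the protocol makes the autoantibody concentrations a secondary endpoint, measured as follows: "Before and after active and sham treatment (before therapy cycle 1/after therapy cycle 1 and before therapy cycle 2/after therapy cycle 2".

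Table 1 (laboratory tests and collection of biomaterial) schedules the antibodies accordingly, for instance "Antibodies against muscarinic acetylcholine receptors of subtypes M1-M4 | E, vT1, nT1, vT2, nT2 | Serum". Its legend keeps three kinds of time point apart: "T1 = during therapy cycle 1; T2 = during therapy cycle 2; vT1 = before therapy cycle 1; nT1 = after therapy cycle 1". Venous blood gas analysis is the one row that uses the T1 and T2 codes. The coagulation tests share the antibody schedule: "Activated partial thromboplastin time (aPTT) | E, vT1, nT1, vT2, nT2 | Citrate plasma", and likewise INR.

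Table 2 also lists sampling during a cycle separately from sampling before and after it. Its blood-sampling row reads "E, T1, nT1, T2, vT2, nT2, F". vT1 is absent there, and the note explains that "for most examinations, the evaluation examination is equivalent to the examination before therapy cycle 1".

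The caption to Table 4 in section 9.4, which covers both inpatient stays, then states that "blood samples indicated above as being taken before or after therapy are taken during extracorporeal therapy to avoid additional punctures".

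Section 9.5 adds that "Anticoagulation is performed during both sham treatment and actual immunoadsorption using heparin". The third amendment changes this to citrate plus heparin, again for both treatments.

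**The concern.** The caption overrides the distinction that the endpoint and the tables draw. It takes samples labelled as before or after therapy and places them during therapy, without giving the session, the moment or the sampling site.

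Only the verum cycle has an adsorber. A before-sample drawn while a verum session is running is already partly depleted, and an after-sample drawn during the last verum session misses what that session still removes. In a sham cycle neither happens. The error therefore does not cancel in the verum-sham comparison, and it works towards understating the fall under verum. Because the moment is not fixed, it may also differ between participants.

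At stake are the endpoint on antibody concentrations, the matching project objective in section 5 (verifying the effect of immunoadsorption on those concentrations), and the stated use of the laboratory values to help explain changes in symptoms. Separately, aPTT and INR drawn with anticoagulant running cannot serve as pre-treatment values, in either cycle.

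**Working it through.** The plan gives no figure on this point to reproduce. The check has two parts.

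**1. The passages side by side**

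- Endpoint (6.2): antibodies before and after each cycle, active and sham.
- Table 1: antibodies at E, vT1, nT1, vT2 and nT2, with no T1 or T2. The code for sampling during a cycle exists and is not used for them.
- Table 2, blood sampling: T1 and T2 stand beside nT1, vT2 and nT2 as separate occasions.
- Table 4 caption: the before- and after-samples are taken during therapy.

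The first three agree with each other and the caption contradicts them. None of the three amendments touches sampling time.

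**2. Size if the caption is followed literally**

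From the protocol: five sessions per cycle, an adsorber only in verum, and 2 to 2.5 L exchanged per session. Assumed, because the documents do not say: each session removes a fraction f of the concentration, removal is log-linear within a session, there is no rebound between sessions, and both samples are drawn midway (session 1 and session 5).

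- True fall over the cycle: 1 − (1 − f)^5.
- Before-value: (1 − f)^0.5 of the true start. After-value: (1 − f)^4.5. Their ratio is (1 − f)^4, so the apparent fall is 1 − (1 − f)^4.

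| f | True fall | Apparent fall |
| --- | --- | --- |
| 0.3 | 1 − 0.7^5 = 83% | 1 − 0.7^4 = 76% |
| 0.5 | 1 − 0.5^5 = 97% | 1 − 0.5^4 = 94% |
| 0.7 | 1 − 0.3^5 = 99.8% | 1 − 0.3^4 = 99.2% |

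If both samples are drawn at the true start and end of treatment, the error is zero. Under sham, f = 0 and adsorption changes neither value at any draw time.

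A second route starts from the protocol's exchange volume V. Assume a plasma volume Vp of 2.5 to 3.5 L, one compartment, complete removal from processed plasma and no rebound. Removal per session is then 1 − exp(−V/Vp):

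- lowest: 1 − exp(−2/3.5) = 44%; highest: 1 − exp(−2.5/2.5) = 63%;
- true fall over five sessions, 1 − exp(−5V/Vp): 94% to 99%;
- apparent fall with both draws midway, 1 − exp(−4V/Vp): 90% to 98%.

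Both routes give a shortfall of a few percentage points, always in the same direction.

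**The case against.** The strongest reply is that the caption was never meant to describe a draw from a running circuit. Its stated reason is to spare punctures, which fits a draw through the therapy access at connection and again at the end of a session. Table 4 also lists the blood sample as its own item ahead of cannulation and the first session. This stands: contamination is a consequence of the literal wording, not an established fact. A reader might infer that the endpoint is certainly measured on partly treated blood, but the documents do not support that, because they fix no moment.

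A second reply is that clean values exist. Antibodies are also scheduled at E, and participants who start with sham have further values before any adsorption. This stands in part. E may be a result carried over from the earlier cohort study rather than a fresh sample, and the endpoint is defined on the vT and nT samples.

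Third, the bias is conservative and small over five sessions. That also stands. A single before-value drawn midway would be low by 1 − √(1 − f), which is 16%, 29% or 45% for f = 0.3, 0.5 or 0.7. A reader might take those figures as the bias in the endpoint. They are not: the endpoint is a before-after comparison, and both samples shift.

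Three further inferences should be resisted:

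- Anticoagulation runs in both treatments, so its effect is not confined to verum.
- Nothing in the documents shows that anticoagulation alters a serum antibody result, so that point is limited to aPTT and INR, which are not endpoints.
- Section 5 names correlations of autoantibodies with symptoms or their severity. It does not name a correlation of antibody change with symptom change.

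**Conclusion.** The contradiction is real and the protocol does not resolve it. The Table 4 caption cannot be reconciled with section 6.2 and the codes in Tables 1 and 2. Followed literally, it understates the fall in autoantibodies under verum and leaves sham unaffected by adsorption. It also puts aPTT and INR under anticoagulation in both cycles.

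The size depends on a draw time that the protocol does not fix. It is nil at connection. With both draws mid-session it is, for example, 76% instead of 83% at 30% removal per session, or 94% instead of 97% at 50%. These figures rest on the assumed log-linear removal without rebound and are illustrative only. They would not hide a substantial fall in autoantibodies.

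No primary endpoint is a blood measure, so only secondary and laboratory measures are affected. Severity: minor.

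**What to change.** Reword the Table 4 caption so that it states the session, moment and site of each draw:

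- The before-sample (vT1, vT2) is drawn from the freshly placed access in session 1 of the cycle, before the circuit and anticoagulation are started.
- The after-sample (nT1, nT2) is drawn from the same access once the last session of the cycle has ended and before the access is removed.
- The rule applies identically to verum and sham cycles.

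This keeps the caption's aim, since no extra puncture is needed, and it brings the caption into line with section 6.2 and Table 1. It concerns sampling only and changes nothing in the treatment. The cost is a short rewording of the caption, a nursing instruction, and a minute or two per cycle.

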## 9.5 Administration of treatment

All study participants receive 5 blinded extracorporeal therapies with the Plasauto Sigma from Diamed with a TR-350 adsorber inserted and 5 extracorporeal therapies with the same device with no adsorbers inserted. The order, i.e., whether the verum treatment (adsorber inserted) or the sham treatment with no adsorbents is performed first, will be assigned randomly. Immunoadsorption and sham treatment are performed, depending on the condition of the veins, via two large-lumen peripheral venous cannulas or, if this is not possible due to poor vein condition, via a Shaldon catheter, which is inserted into the right or left internal jugular vein under ultrasound guidance after the patient has been informed of the risks and has given their consent. Anticoagulation is performed during both sham treatment and actual immunoadsorption using heparin (bolus of 2000iE, then flow rate of 2000iE/h) and the PA-420 tube system is used. The blood flow is set to 60 ml/min and the plasma flow to 20ml/min for both therapies. The exchange volume depends on the patient's size and body weight and is 2-2.5 L per session.

## 9.6 Total duration of the study

The total duration of the study is set at 24 months. This study duration is based on the fact that 40 participants are to be recruited and then treated. One treatment cycle lasts one week. Each participant receives two treatment cycles, so that two weeks of pure therapy must be calculated per participant. Since the capacity for extracorporeal procedures at the study center is limited, this long period of time is necessary to be able to carry out a sufficient number of therapies. Twenty months are therefore scheduled for the therapy, two months for the necessary preliminary examinations and study inclusion, and two months for the follow-up visits.

## **Benefit-risk assessment**

10.1 Individual benefits associated with participation in the study

- Detailed examination and objectification of the symptoms and severity of post-COVID syndrome
- Investigation of alternative causes for the symptoms and associated findings about the individual's state of health
- Advice on further treatment options in the event of a diagnosis of a disease within the scope of the study examination
- Prospect of symptom relief if the investigated immunoadsorption is effective in post-COVID

10.2 Burdens and risks associated with participation in the study

- Pain, hematomas, accidental arterial puncture, damage to peripheral nerves during peripheral venous cannulation before each immunoadsorption or sham adsorption, reduction of risk through ultrasound-guided cannulation
- Insertion of a central venous dialysis catheter (Shaldon catheter) if peripheral venous cannulation is not possible, with risk of injury to the carotid artery, bloodstream infections, risk of lung injury with development of pneumothorax Reduction of risks through sterile working practices, ultrasound-guided catheter placement, and the extensive experience of the physicians involved in the study in catheter placement
- Allergic reaction to heparin, adsorbent material, or tubing materials
- Development of heparin-induced thrombocytopenia (HIT) with the development of thromboembolism, a drop in platelet concentration, and the development of bleeding
- Stress caused by two hospital stays of 7 days each

10.3 Discontinuation criteria

- Participation in the study is voluntary. Patients may withdraw from the study at any time without giving a reason and without any subsequent disadvantage.
- Definition of adverse events (AE): Adverse events are defined as any disturbances in well-being observed during the course of treatment.
- Serious adverse event (SAE): An SAE is life-threatening or fatal. It leads to significant or persistent disability, hospitalization, and includes any significant risk that may harm the patient and is related to the treatment administered.
- Non-serious adverse event (AE): All events that do not fall under the SAE category.

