## **Version date:** February 27, 2022

## **Summary of the project**

| Study title | Mainz Immunoadsorption Study in Adults with Post-COVID (IAMPOCO) |
| --- | --- |
| Applic | [name], MD |
| Study location | Main |
| Fund | Third-party funding (Diamed Medizintechnik, Cologne, Germany) |
| Study design/type | Prospective randomized single-blind placebo-controlled study |
| Number of subjects | 40 subjects |
| Study population | Adults recruited from participants in the Gutenberg Post-COVID Study who had at least one positive SARS-CoV-2 PCR test at least 6 months prior to study inclusion, as well as new or persistent symptoms of SARS-CoV-2 infection 3 months after a positive PCR test that have persisted for at least 2 months. |
| Planned start of study | March 8, 2023 |
| Study duration per subject | 4.5 |
| Planned study duration | Recruitment period: 6 months  Duration of the clinical study: 18 months |
| Primary endpoint | Effectiveness of immunoadsorption on symptom burden in patients with post-COVID syndrome as measured by the values of:   - Post-COVID-19 Functional Status Scale (PCFS) - Chalder Fatigue Scale - Montreal Cognitive Assessment (MOCA) - MFI-20 - Bell Score - Strength measurement   And their comparison before and after verum therapy and before and after sham therapy (before therapy cycle 1/after therapy cycle 1 and before therapy cycle 2/after therapy cycle 2) |

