| Secondary endpoints | 1. Frequency of adverse events under active and sham treatment  2. Prevalence of anti-adrenergic and anti-muscarinic autoantibodies in patients with post-COVID syndrome:   - Proportion of subjects with evidence of anti-α1-adrenoreceptor AK - Proportion of subjects with evidence of anti-α2-adrenergic receptor antibodies - Proportion of subjects with evidence of anti-β1-adrenoreceptor AK - Proportion of subjects with evidence of anti-β2-adrenoreceptor AK - Proportion of subjects with evidence of anti-β3-adrenoreceptor AK - Proportion of subjects with evidence of anti-M1 acetylcholine receptor AK - Proportion of subjects with evidence of anti-M2 acetylcholine receptor AK - Proportion of subjects with evidence of anti-M3 acetylcholine receptor AK - Proportion of subjects with evidence of anti-M4 acetylcholine receptor AK  1. Concentration of:  - Anti-α1 adrenoreceptor AK - Anti-α2-adrenoreceptor AK - Anti-β1 adrenoreceptor AK - Anti-β1 adrenoreceptor AK - Anti-β1-adrenoreceptor AK - Anti-M1 acetylcholine receptor AK - Anti-M2 acetylcholine receptor AK - Anti-M3 acetylcholine receptor AK - Anti-M4 acetylcholine receptor AK   Before and after treatment with active substance and placebo (before therapy cycle 1/after therapy cycle 1 and before therapy cycle 2/after therapy cycle 2) |
| Safety parameters | Not applicable |

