## **Study design**

The Mainz immunoadsorption study in adults with post-COVID is a single-center, randomized, controlled, single-blind study with a cross-over design that aims to investigate the potential effect of immunoadsorption therapy on symptom burden in people with post-COVID. The study is being conducted by an interdisciplinary team of investigators.

Included subjects are first randomized to receive either 5 verum treatments (immunoadsorption with TR-350 adsorber) or 5 sham treatments (connection to the Plasauto Sigma without adsorber). All subjects will receive both the real treatment and the sham treatment unless they decide against the respective therapy cycle before the start of the respective therapy cycle. Randomization is only used to determine which treatment is given first.

Participating subjects may withdraw from the study at any time, including after the first therapy cycle or before the second therapy cycle.

The subjects are blinded because they do not know whether the treatment is being carried out with or without an adsorber, and it is also not apparent to the subjects, as the TR-350 adsorber and Plasauto Sigma are set up behind a curtain that is not visible to the patient and remain there throughout the treatment.

The blinding of the subjects serves to assess the actual effect of the therapy without the influence of the therapy arm on the patients' reports. Since the therapeutic effects in the present study are predominantly measured using self-report instruments, such an approach seems essential to minimize the influence of distortions caused by psychological effects of the verum therapy on the study results.

[figure not shown]

1 Figure Study design and flow chart

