## **Study population**

### 8.1 Inclusion criteria:

- Fulfilment of the WHO diagnostic criteria for post-COVID syndrome
- Written consent to participate in the study
- Previous participation in the Gutenberg Post-COVID study
- Minimum age of 18
- PCFS score of at least 2

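### The adverse-event definition does not require an event to be new or worse, so persisting post-COVID symptoms dilute and may mask the verum–sham comparison of adverse-event frequency

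*Protocol*

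**What the plan says.** Section 10.3 gives the only counting rule: "Adverse events are defined as any disturbances in well-being observed during the course of treatment". The bullet on non-serious events does not narrow it: "Non-serious adverse event (AE): All events that do not fall under the SAE category". Only the bullet on serious events mentions a relation to treatment.

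The rule feeds a named secondary endpoint in section 6.2: "Frequency of adverse events under active and sham treatment". The safety row of the project summary reads "Safety parameters | Not applicable", so no narrower definition is found there.

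Participants are symptomatic by design. Section 8.1 requires "Fulfilment of the WHO diagnostic criteria for post-COVID syndrome" and "PCFS score of at least 2". The project summary describes "new or persistent symptoms of SARS-CoV-2 infection 3 months after a positive PCR test that have persisted for at least 2 months". The design is a cross-over: "All subjects will receive both the real treatment and the sham treatment unless they decide against the respective therapy cycle".

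**The concern.** A definition without an onset or worsening condition cannot separate what the procedure does from what the patient brought along. The background section names fatigue, memory problems, dyspnoea, sleep disorders and joint pain as the most common complaints. Each is a disturbance in well-being, and if it persists it can be observed during both cycles of the same patient.

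Two things are at stake. First, the comparison of adverse-event frequency loses contrast, because the same complaints are added on both sides. Second, the counted complaints overlap with the primary outcomes in section 6.1 (PCFS, Chalder, MFI-20, Bell). If verum relieves symptoms, its adverse-event count falls for that reason and can offset procedural harm, so benefit and harm end up in one number.

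**Working it through.** **Inputs.** The protocol gives no adverse-event rate, difference or power. Its only power figure is for the MoCA (19 per group, 90% power, effect size 1.0, one-sided 0.05). That figure reproduces: a t-test calculation gives 18 per group, and applying the Wilcoxon efficiency 3/π gives 19, with power 0.904. It has no bearing on adverse events. From the protocol I use N = 40 and the cross-over design. All event rates below are assumptions.

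**1. Frequency read as the proportion of patients with at least one event per cycle.** Let b be the fraction of patients who score in both cycles from the disease alone, and let s and v be the probabilities of a treatment-caused event under sham and verum.

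- Observed proportions: p = 1 − (1 − b)(1 − s) under sham and 1 − (1 − b)(1 − v) under verum.
- Observed difference: (1 − b)(v − s).
- Discordant pairs for McNemar's test: (1 − b)·v·(1 − s) and (1 − b)·s·(1 − v).

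With s = 0.10, v = 0.40, and simulated power of the two-sided exact McNemar test:

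| b | sham | verum | difference | power |
|---|---|---|---|---|
| 0 | 10% | 40% | 30 points | 0.84 |
| 0.5 | 55% | 70% | 15 points | 0.42 |
| 0.8 | 82% | 88% | 6 points | 0.04 |
| 1 | 100% | 100% | 0 | 0 |

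**2. Frequency read as the number of events per cycle.** Let k be the number of persisting complaints per patient, equal in both cycles, with assumed emergent means of 0.50 (verum) and 0.25 (sham).

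- Difference: (k + 0.50) − (k + 0.25) = 0.25 for every k.
- Ratio: (k + 0.50)/(k + 0.25), which is 2.00 at k = 0, 1.50/1.25 = 1.20 at k = 1, 3.50/3.25 = 1.08 at k = 3 and 5.50/5.25 = 1.05 at k = 5.

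**3. Noise in the counts.** If the background count varies from cycle to cycle, it adds variance. With independent Poisson counts, emergent means of 0.5 (sham) and 1.0 (verum) and background mean λ, the standard error of the mean difference is √((0.5 + 1.0 + 2λ)/40). Power is 1 − Φ(1.96 − 0.5/SE).

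- λ = 0: SE 0.194, ratio 2.0, power 0.73.
- λ = 2: SE 0.371, ratio 1.2, power 0.27.
- λ = 10: SE 0.733, ratio 1.05, power 0.10.

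This is the unfavourable end. A complaint that is identical in both cycles of a patient cancels in the within-patient difference and adds no noise.

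**4. Relief mixed with harm.** Take the rates of step 2 with one background complaint under sham: the sham count is 1 + 0.25 = 1.25. If verum lowers the background by 0.25, its count is 0.75 + 0.50 = 1.25. The excess of 0.25 emergent events disappears even from the absolute difference.

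**The case against.** The strongest reply is that the words can be read more narrowly. A disturbance observed during treatment may mean something that happens then, not something that merely continues. The context lends support: section 10.2, just before, lists procedural harms, and post-COVID symptoms are captured separately as primary outcomes. Nothing tells staff to log unchanged fatigue as an event. This reading is possible, but the text does not state it, and one clause would settle the matter.

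A second reply is that the choice of events to compare belongs in a statistical analysis plan, which is not shown. That holds for whether patients or events are counted. It does not hold for the definition, which the protocol fixes itself and which governs what is recorded. A later plan can filter on onset or worsening only if that was captured.

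A reader might infer that the rule hides any verum–sham difference, with all patients scoring under both treatments. The documents do not support that. Section 6.2 says only frequency. Complete masking needs a proportion of patients, with nearly all of them scoring from the disease alone. The PCFS threshold is an entry criterion and is not required again on treatment days or before cycle 2. Under event counts the absolute difference survives if the background is equal, and a haematoma or allergic reaction stays visible if events are listed by type.

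Nor should the summary's safety row be read as an absence of all other safety data. Serious events are defined separately, vital signs are monitored in every session, and laboratory values are taken before and after each cycle. None of this repairs the adverse-event endpoint itself.

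**Conclusion.** The point holds as a badly fixed definition. Taken literally, section 10.3 counts persisting post-COVID complaints under both treatments. It therefore dilutes and may mask the comparison in section 6.2, and it lets symptom relief enter the harm count.

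The direction follows from the text; the size does not. The loss in a difference of proportions is the factor (1 − b), and b is unknown: it could be small if staff apply the narrow reading, or large if they follow the words. For counts, the loss lies in the ratio and, where complaints fluctuate, in precision. The endpoint is secondary and the correction is cheap, so this should be changed but does not undermine the trial as a whole.

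**What to change.** In section 10.3, define an adverse event as a disturbance in well-being that is new, or worse than the status recorded before the same therapy cycle: the evaluation or pre-cycle-1 status for cycle 1, and the vT2 status for cycle 2. In section 6.2, count the endpoint on that basis, by cycle and treatment. Keep unchanged post-COVID complaints as baseline conditions.

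The cost is small but is more than a sentence.

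- **Reference for cycle 1.** Table 2 lists no vT1 assessment for PCFS, Chalder, Bell or MRC. Its note treats the evaluation as equivalent for most examinations, while the Chalder and Bell descriptions place them before cycle 1. The revised text should name the reference it uses.
- **Ongoing complaints.** The existing scales do not cover every symptom (none is described as recording sleep, for example), so staff need to note ongoing complaints at the start of each cycle.
- **Judgement of worsening.** Staff must decide whether a complaint is worse than before. Only the subjects are described as blinded, so the pre-cycle status should be written down before the first session.
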